#### Randomization of Ankle-Foot Device Selection and Order of Evaluation

The ankle-foot devices for each participant and the order in which they will be evaluated will be block randomized using a computer-generated algorithm that randomly selects from all available devices and then assigns the order. The randomization will be performed before study enrollment, so that each combination of device order is used an equal number of times. Investigators who process and evaluate the data will be blinded to the data. Owing to the distinct differences between prosthetic ankle-foot devices, the participants and study prosthetists cannot be blinded to which foot is assigned.

#### Visit 2—Static Fitting, Dynamic Fitting, and Prosthetic Alignment

Participants will return to the prosthetic clinic for fitting of the definitive sockets and prostheses by the study prosthetist. Another subjective pain VAS measurement will be performed at the beginning of the fitting visit, before the participant returns home with an ankle-foot device. All prostheses will initially be bench aligned based on the manufacturer’s specifications for a static fitting. After successful static fitting is achieved, the dynamic alignment of each prosthesis will occur. The participant will separately ambulate with each of the prostheses, and adjustments will be made to the alignment, as needed, to achieve an optimal gait pattern, as determined by the study prosthetist and physical therapist. Dynamic fitting may require multiple visits, and participants will progress to the next part of the study protocol after an appropriate dynamic alignment has been established.

#### Device-Specific Training to Meet a Minimum Standard of Performance

After appropriate fit and alignment of each prosthesis has been established using each ankle-foot device, all participants (100/100, 100%) will undergo device-specific training by a qualified clinician to meet a minimum standard of functional performance. Overall, 2 aspects of the Functional Independence Measure will be evaluated: the ability to walk over level ground and the ability to ascend and descend stairs. To advance in the study, the participant must score 6 (modified independence) or 7 (complete independence) on the Functional Independence Measure. If the participant fails to achieve this outcome, guided rehabilitation to enhance the participant’s use of their ankle-foot device will be provided until they are able to meet the minimum standard of performance. The process of device-specific training may require multiple visits. When the minimum standard of performance is met, participants will return home with the first randomized ankle-foot device for a 1-week acclimation period.

#### Description of the Physical Therapy Plan If the Minimum Standard of Performance Is Not Met

Participants who do not meet the minimum standard of performance using a study ankle-foot device will complete a series of physical therapy training sessions lasting 30 to 45 minutes each during the training period, completing 2 sessions per week, on average. Sessions 1 and 2 will specifically focus on education, strengthening through therapeutic exercises, and early neuromuscular re-education. A home exercise program will be initiated with the participant during the initial sessions and progressed along with the program. Sessions 3 and 4 will include gait training on level surfaces. Sessions 5 and 6 will include continued progression in all areas, including multidirectional training for both neuromuscular re-education and gait. Training will conclude with sessions 7 and 8, during which the previously taught skills will be further challenged and mastered. In addition, advanced gait skills, such as ambulation on stairs and ramps, will be covered. If a participant is unable to meet the minimum standard of performance after receiving physical therapy, they will be unenrolled from the study, as determined by the study physical therapist.

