**Inclusion criteria**
Veteran, service member, or civilian with unilateral transtibial limb lossUses a prosthesis with a well-fitting socket for a minimum of 1 monthMust achieve at least modified independence score on the Functional Independence Measure for the 2 mobility items (locomotion and stairs)Aged >18 yearsCurrent use of an energy storing and returning deviceHas a minimum clearance to accommodate all devices

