ESR (nonarticulating)—This group includes any qualifying nonarticulating ESR ankle-foot device that is commercially available. As per the inclusion criteria, participants will use their current device for this category. There are >100 commercially available devices that fit the criteria for this category [5].Active plantarflexion ESR (PWR)—This group will include all commercially available ESR ankle-foot devices with active plantarflexion. Currently, Empower (Ottobock Inc) is the only device classified into the PWR group. No new devices that meet the criteria for the PWR group will be included in this investigation after the commencement of active enrollment. However, it is not anticipated that any future powered device will come to the market during active enrollment.ART—This group includes all current, commercially available options in the K3 Medicare Functional Classification System category that have an articulating ankle and ESR properties. Overall, 14 devices that met the criteria were identified at the time of study initiation (Table 1). No new devices that meet the criteria for the ART group will be included in this investigation after the commencement of active enrollment. If any ART device is replaced by the manufacturer with a new generation during active enrollment, the study expert panel will determine whether the new generation can be considered as a replacement device (if not fundamentally distinct). If the new generation of ART device is considered to be fundamentally different from the study ART device by the expert panel, it will not be included as a study device, to reduce confounding variables during analysis. However, the current generation of ART device used in the investigation will be configured to match patient specifications for any future participant who is assigned that ART device.

**Table 1 table1:** Articulating energy storing and returning ankle-foot devices included in the study.

Manufacturer	Device
Blatchford	Echelon
Blatchford	EchelonVT
Blatchford	Elan
Fillauer	Motion Foot
Proteor	Kinnex
Proteor	Kinterra
Ossur	Proprio
Ossur	Flex-Foot Balance
Ossur	Proflex Pivot
Hosmer	Raize
College Park	Odyssey K3
College Park	Trustep
College Park	Tribute
College Park	Venture

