### Justification for Inclusion of Commercially Available ESR Ankle-Foot Devices

#### ESR Group

Many nonarticulating ESR prosthetic ankle-foot devices have different mechanical features (eg, torsion and vertical shock) that provide for specific Healthcare Common Procedure Coding System classifications, as descried in the *Prosthetic Foot Project* conducted by the American Orthotic and Prosthetic Association [31]. Although subtle mechanical differences may exist between these ankle-foot devices, studies so far have not shown any significant differences in functional outcomes between different nonarticulating ESR ankle-foot devices [32]. More specifically, published literature often reports contradictory results regarding biomechanics and function during level ground ambulation, stair negotiation, and incline and decline ambulation using these ESR ankle-foot devices [15]. Clinical consensus has also shown that patients may have individual preferences for specific nonarticulating ESR ankle-foot devices, but there is no current metric to predict this. Limiting the investigation to one or just a few nonarticulating ESR ankle-foot devices would limit the generalizability of the findings to the overall group of ESR ankle-foot devices. In addition, most patients who ultimately enroll in this investigation often have the opportunity to trial many different ankle-foot devices as part of their standard clinical care, given that prescription is not driven by reimbursement rates within VA and the DoD. For example, the limb loss care teams at VA and the DoD are not required to abide by the Medicare Functional Classification System for prosthetic prescription and can prescribe any device deemed clinically beneficial for veterans and service members. Therefore, the ESR ankle-foot device the participant enrolls with may be their foot of preference within the overall nonarticulating ESR category. Furthermore, prosthetic devices frequently change, update, or can even be taken off the market for another generation of device. Limiting the ESR ankle-foot devices may also risk not investigating the current or future prescription trends in the limb loss care clinics at all 4 study sites.

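### Unenrolling people who cannot reach the minimum standard with a study foot leaves device failures out of the results and, relative to the eligible population, tends to favor ART and PWR over ESR

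*Protocol article*

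**What the plan says.** Four parts of the protocol article bear on this point.

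- **The rule.** The section on the physical therapy plan says: "Participants who do not meet the minimum standard of performance using a study ankle-foot device will complete a series of physical therapy training sessions". It sets out eight sessions and continues: "If a participant is unable to meet the minimum standard of performance after receiving physical therapy, they will be unenrolled from the study". The decision lies with the study physical therapist.
- **The standard.** Device-Specific Training says: "To advance in the study, the participant must score 6 (modified independence) or 7 (complete independence) on the Functional Independence Measure". The items are level walking and stairs. The same section offers guided rehabilitation until the standard is reached and mentions no exit.
- **Entry.** The inclusion criteria require that a participant "achieve at least modified independence score on the Functional Independence Measure" for locomotion and stairs, and currently uses an ESR device. Ankle-Foot Categorization says of the ESR group: "As per the inclusion criteria, participants will use their current device for this category". The ESR Group section adds that "the ESR ankle-foot device the participant enrolls with may be their foot of preference within the overall nonarticulating ESR category".
- **Timing and use.** On randomization: "The randomization will be performed before study enrollment, so that each combination of device order is used an equal number of times". Participants take the first foot home only once the standard is met, and outcomes begin at visit 3. Statistical Analysis ranks the devices within each participant. Development of Prediction Model regresses preferred prosthesis on several domains. Neither section mentions participants who failed the standard.

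**The concern.** The trial seeks criteria for which foot suits whom. A person who cannot walk and climb stairs at the required level with a given category, even after therapy, is direct evidence for such criteria. Under the stated rule that person leaves the study, and the article does not count the event as a result. Whether someone remains in the comparison therefore depends partly on how the tested devices perform, and that dependence appears to run one way, against people who do badly with ART or PWR. A guideline built on those who remain could make these categories look more widely suitable than they are among the patients a clinic would consider for them.

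**Working it through.** The article gives no figure for this point, so there is none to reproduce. Steps 1 to 3 compare sections; step 4 shows what the size could be.

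**1. When the rule acts.** The order schedule exists before enrollment. Fitting and training with each foot come next, then the first take-home week, then outcomes at visits 3 to 5. Removal therefore follows randomization and precedes every device outcome.

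**2. Which feet can trigger it.** The threshold for advancing (FIM 6 or 7 on walking and stairs) equals the entry threshold (at least modified independence on the same two items). Participants enter as ESR users, and their own foot is the ESR condition. Failures with ESR are thus largely screened out at entry, leaving ART and PWR as the likely sources. The criteria do not say which foot was worn for the entry FIM; that it was the current ESR foot is an inference, though a natural one.

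**3. What is lost.** An unenrolled participant has baseline data and the fact of the failure, but no functional, survey, step-activity or preference data on any foot.

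**4. Possible size.** Let D be a participant's difference, ART or PWR minus ESR, normal with true mean 0 in all eligible participants. Suppose the lowest fraction f on a latent score for coping with the device is removed, and that score has correlation r with D. The mean of D among those remaining shifts by

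shift in SD units = r × φ(z_f) / (1 − f).

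Neither f nor r is in the documents; both are assumptions. The factor φ(z_f)/(1 − f) is 0.049, 0.109, 0.195 and 0.350 at f = 2%, 5%, 10% and 20%. Products below come from unrounded factors.

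| Removed | r = 0.3 | r = 0.5 | r = 0.8 |
|---|---|---|---|
| 2% | 0.01 | 0.02 | 0.04 |
| 5% | 0.03 | 0.05 | 0.09 |
| 10% | 0.06 | 0.10 | 0.16 |
| 20% | 0.10 | 0.17 | 0.28 |

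*In metres.* Table 2 gives 61 m as the SD for 6-minute walk distance. If that were the SD of paired differences, r = 0.5 would give 1.5, 3.3, 5.9 and 10.7 m. The text calls the SDs within-group, however. If 61 m is a group SD and the within-person correlation is 0.8 (assumption), the paired SD is 61 × √(2 × 0.2) ≈ 39 m, and the shifts fall to about 1, 2, 4 and 7 m. SD units are the safer scale.

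*Preference.* Suppose 40% of all eligible participants would prefer ART or PWR and none of those removed would. The observed share is 0.40/(1 − f): 40.8%, 42.1%, 44.4% and 50.0%. This is an extreme case, since someone who fails with one of the two might still prefer the other.

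**The case against.** The strongest reply is that the rule is a gate before outcomes. No device data exist at that point, so none are deleted, and in a crossover the within-participant contrasts are valid for everyone who passes. The bar is modest, participants already meet it with ESR, and up to eight sessions are offered, so failures may be few. Analysis sets and missing-device handling may also be set out in a full protocol or analysis plan that is not shown.

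Most of this stands. A reader might infer that the rule discards collected data on three devices; the sequence of visits shows otherwise. A reader might also infer that the trial's false-positive rate is inflated. A shift counts as an error only if the target is all eligible persons; among people able to use all three feet, the shifted mean is the true mean. Any such error rate would also rest on a failure rate that the documents do not give.

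The reply does not remove the point. The article states the removal rule itself, and outcomes never collected cannot be recovered by an analysis plan. The stated aim is prescription criteria for the three categories, and people who cannot use one of them belong to that question.

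**Conclusion.** The point holds as one of scope and reporting. As written, the results will describe people able to reach the standard with all three feet. Relative to the eligible population, ART and PWR will tend to look better against ESR than they are. That direction rests on the shared FIM threshold and on the ESR condition being the participant's own foot. The size cannot be stated: at r = 0.5 it runs from about 0.02 SD with 2% failures to 0.17 SD with 20%, and it is negligible if failures are rare. The direction for ART against PWR is not determined, because it depends on which of the two people fail with more often.

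Separately, the two sections disagree on what follows a failure: one offers rehabilitation until the standard is reached, the other eight sessions and then unenrollment.

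**What to change.** 1. Record every failure to reach the standard by device and category. Report it as a device-level outcome with a 95% CI, out of all participants fitted with that category.
2. In the ranking and preference analyses, at least as a sensitivity analysis, keep these participants with their baseline data and rank the failed device last. Their order among the other feet stays missing.
3. State that the remaining comparisons apply to people who reached the standard with all three feet.
4. Reconcile Device-Specific Training with the physical therapy plan on what happens when the standard is not reached.

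The cost is wording, one recorded item per device, and a few participants with incomplete data. Items 1 to 3 need no further visits and leave the training and withdrawal rule as it is. Obtaining outcomes on the other feet from people who failed with one would require them to stay enrolled; that would change participant flow and is not proposed here.

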#### Visits 3 to 5—Functional Assessment of ESR, ART, and PWR Ankle-Foot Devices

Visit 3 will begin after the 1-week acclimation period while using the first assigned ankle-foot device. Participants will complete the VAS pain scale and then a battery of outcome measures and surveys (outlined in the following sections). In addition, during visit 3, a subset of participants will also be randomized to undergo biomechanical gait analysis while using the first prosthesis (described in the following sections). Once visit 3 is completed, the participant will receive the second prosthesis according to the established randomization schedule, and the initial prosthesis will be returned to the study prosthetist. The participant will again complete a 1-week acclimation period. During visit 4, the participant will undergo the same pain scale and battery of outcome measures and surveys. The same subset of participants will also undergo biomechanical gait analysis using the second prosthesis. The third prosthesis will be issued at the end of visit 4, and the second prosthesis will be returned to the study prosthetist. Participants will receive the same 1-week acclimation and will complete the same pain scale and battery of outcome measures and surveys during visit 5. In addition, the same subset of participants will undergo biomechanical gait analysis while using the third prosthesis. For visits 3 to 5, a visit window of –2 to +2 days will be implemented.

#### Functional and Subjective Outcome Measures

The functional and subjective outcome measures were selected to optimize relevance to the participant population, providers, and health care systems. These measures are commonly used in prosthetic clinics and represent critical information in the functional and subjective domains needed to develop guidelines for prescription. Following the completion of the investigation, the selected outcome measures will be statistically analyzed to determine which measures are the most sensitive to changes in device type. The battery of functional outcome measures and subjective surveys collected after each acclimation period will be administered by a local research team member. Functional outcome measures include the 6-Minute Walk Test, Timed-Up-and-Go, Four Square Step Test, Amputee Mobility Predictor, Stair Assessment Index, and Hill Assessment Index. Surveys include the Prosthesis Evaluation Questionnaire, Short Form-12, and Orthotics and Prosthetics Users Survey. These measures are described in Textbox 2.

Measures included in the study.
**6-Minute Walk Test (6MWT)**
6MWT measures the distance an individual can walk in 6 minutes without help or encouragement. The 6MWT is a valid and reliable metric that correlates with physical function and functional capacity [34] and has good interrater and intrarater reliability in individuals with lower limb loss [34].
**Timed-Up-and-Go (TUG)**
TUG measures the time taken by an individual to stand up from a standard armchair, walk 10 feet, turn, walk back to the chair, and sit down. The TUG is both reliable and valid in individuals with lower limb loss [35]. In addition, the TUG has also been used as a measure to determine risk of falling [36] and correlates well with other measures of physical functioning [37].
**Four Square Step Test**
Four Square Step Test is a high-order, complex task assessing dynamic balance and has been validated for use in individuals with lower limb loss [38,39].
**Amputee Mobility Predictor**
Amputee Mobility Predictor is a 21-item instrument designed to measure basic prosthetic mobility of individuals with lower limb loss [40].
**Hill Assessment Index**
Hill Assessment Index is a rated, qualitative scale on how an individual with lower limb loss negotiates up and down an incline [41]. This will be performed on a standardized ramp (rise-to-run ratio of 1:6) with a minimum length of 4.9 m to allow for sufficient number of steps to be taken by the participant.
**Stair Assessment Index**
Stair Assessment Index is a rated, qualitative scale for stair negotiation for individuals with lower limb loss [41]. This assessment will be performed while participants ambulate on at least 4 steps that are compliant with the Americans with Disabilities Act (17 cm high, 28 cm long, and 91 cm wide).
**Prosthesis Evaluation Questionnaire (PEQ)**
PEQ is self-report, visual analog scale–style questionnaire for individuals with lower limb loss who use a prosthesis. It is used to evaluate the prosthesis and life with the prosthesis. It consists of 82 items with 9 functional domain scales, including ambulation, residual limb health, utility, appearance, sounds, frustration, perceived response, social burden, and well-being. The PEQ also contains items beyond the subscales, including satisfaction, pain, transfers, prosthetic care, self-efficacy, and importance [42].
**Short Form-12**
Short Form-12 is a non–disease-specific survey that can be used to measure the relationship between physical and mental health functioning and the social determinants of health [43].
**Orthotics and Prosthetics Users Survey**
Orthotics and Prosthetics Users Survey is a set of self-report instruments that assess functional status, quality of life, and satisfaction with prosthetic devices and services that can be used in prosthetic clinics [44].

#### Visit 6—Home-Based and Community-Based Assessment

After the completion of visits 1 to 5, participants will return home with all 3 prostheses for a period of 30 days, to assess performance and preference during home-based and community-based conditions. All 3 prostheses will be fitted with a Modus Health StepWatch 3 (Modus Health LLC), which is a research-grade instrument for long-term assessment of ambulatory activity during day-to-day life [45,46]. Capturing prosthetic performance while navigating home-based and community-based environments is a key piece of information that is yet to be effectively used in the prescription process [47]. Activity monitoring devices, such as the Modus Health StepWatch 3 used in this investigation, offer the potential to capture this critical information owing to their accuracy for those ambulating with a prosthesis [48]. Participants will also complete an activity log to document their daily activities to allow for correlation between the prosthesis used and activity. Participants are free to use each prosthesis as they choose. Ankle-foot device preference will be based upon total activity time for each prosthesis. Following 30 days of home-based and community-based use, participants will return to the prosthetic clinic to complete a closeout, guided interview to assess subjective preferences. A visit window of –5 to +5 days will be implemented for the final visit.

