**Methods:**

This investigation will be a multisite, randomized, crossover clinical trial targeting the enrollment of 100 participants. Participants will use 3 different types of prosthetic devices (energy storing and returning, articulating, and powered) in random order. Participants will be fitted and trained with each device and then separately use each device for a 1-week acclimation period. Following each 1-week acclimation period, participants will be evaluated using several functional measures and subjective surveys. A random subset of participants (30/100, 30%) will also undergo full-body gait analysis, following each 1-week acclimation period, to collect biomechanical data during level ground and incline and decline walking. After all individual device evaluations, participants will be given all 3 prostheses concurrently for 4 weeks of home and community use to capture user preference. Activity monitoring and a guided interview will be used to determine overall user preference.

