## Methods

### Study Overview

This investigation will be a prospective, multicenter study**,** including 4 sites: Veterans Affairs New York Harbor Healthcare System (VANYHHS), Veterans Affairs Puget Sound Healthcare System, James A Haley Veterans’ Hospital (JAHVH), and Walter Reed National Military Medical Center (WRNMMC). Enrollment began in 2018, and data collection is expected to be completed in 2023. A total of 100 participants will be enrolled from the 4 sites. Briefly, participants will use 3 different types of prosthetic ankle-foot devices (refer to device categorization in the following sections) with duplicate sockets. Participants will be fitted and trained with each device and then separately use each ankle-foot device for a 1-week acclimation period. Participants will only use the assigned study device for each acclimation period. Although previously reported acclimation periods for lower extremity prosthetic device studies have ranged from minutes to months depending on componentry [27-30], this study will use a 1-week acclimation period to balance the time that participants need to adjust to the features of each ankle-foot device with the overall duration of their participation. To augment the acclimation period, device-specific training will be provided to ensure that participants meet a minimum standard of performance. Following each 1-week acclimation period, participants will be evaluated in the laboratory using several functional and subjective measures. Furthermore, a subset of participants (30/100, 30%) will be randomly chosen to undergo a full gait analysis to collect biomechanical data during level ground and incline and decline walking using each ankle-foot device. Following the 3-week data collection period, participants will be given all 3 prostheses at the same time for 30 days to use at home and in their community. Step activity monitoring during home-based and community-based use and a final guided interview will be used to determine overall user preference.

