### Development of Prediction Model

To develop evidence-based guidelines for the prescription of prosthetic ankle-foot devices, the goal of this investigation is to determine which factors and outcomes are the most predictive of optimal performance to meet patient goals. To do this, initial analyses will consist of bivariate cross-tabulations, performed using chi-square analyses. Variable selection for the multivariate model will be informed by these bivariate findings. Logistic regression will then be performed with participants’ preference of prosthesis regressed on each of several domains (eg, functional levels and outcomes, activity levels, and biomechanical parameters). The models will simultaneously control for multiple variables, and overall model predictive value will be assessed using the C-statistic. Domain-specific models (based on bivariate findings) and 1 parsimonious stepwise logistic regression model combining the domains will be created to determine whether each distinct component predicts optimal prescription outcome. Each domain-specific model will control for the identified confounding factors. The individual variables of each domain will be used as fixed predictors. Finally, stepwise multiple regression will be used to determine the factors and outcomes that represent the best predictors, which will be conducted through a series of domain-specific, forward regression models. The significant variables in the forward selection models will then be placed in a backward regression model. Significant variables from the backward regression will be considered as the strongest predictive factors and used to develop prosthetic prescription guidelines.

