**Functional outcome measures**			
	Steps at high activity (%)	9 (13.1)	74.4
	6-minute walk distance (m)	60 (61)	96.3

^a^PEQ: Prosthesis Evaluation Questionnaire.

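### Preference, the outcome of the prediction model, is defined in two ways, and one of them draws on the same 30 days that appear to supply the activity predictors

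*Protocol article*

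**What the plan says.** Three places in the protocol article say how preference is determined.

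- Visit 6, the 30-day period in which participants hold all three prostheses and choose freely among them: "Ankle-foot device preference will be based upon total activity time for each prosthesis". The same section gives the interview its own task: "participants will return to the prosthetic clinic to complete a closeout, guided interview to assess subjective preferences".
- Abstract, Methods: "Activity monitoring and a guided interview will be used to determine overall user preference".
- Study Overview: "Step activity monitoring during home-based and community-based use and a final guided interview will be used to determine overall user preference".

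The Development of Prediction Model section then fits logistic regressions with "participants’ preference of prosthesis regressed on each of several domains (eg, functional levels and outcomes, activity levels, and biomechanical parameters". It adds that "1 parsimonious stepwise logistic regression model combining the domains will be created". Performance is judged by the C-statistic, and variables that survive forward and then backward selection become the basis of the prescription guidelines.

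On activity data, the Visit 6 section describes a step monitor on each of the three prostheses and a daily activity log, both for the 30-day period. The battery for visits 3 to 5 (Functional and Subjective Outcome Measures) contains no activity monitor. Table 2 nevertheless lists "Steps at high activity" among its functional outcome measures (difference 9, SD 13.1, power 74.4%).

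**The concern.** Preference is the dependent variable of the model that is meant to produce the guidelines, which are the study's stated goal. Two things about it are unsettled.

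First, the Visit 6 section rests device preference on activity time alone, while the Abstract and Study Overview rest overall preference on activity and interview together. Nothing in the article says which of these the regression uses, or what happens when a participant wears one foot most and names another in the interview.

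Second, under the activity-time definition the outcome is calculated from the 30-day record, and that record is the only source the article describes for the activity predictors. A variable that measures how much a given foot was used in those 30 days is then close to a restatement of the outcome. It would raise the C-statistic, and stepwise selection would tend to keep it. It would also be of no use to a prescriber, since it is known only after the patient has lived with all three feet.

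A related point concerns high-activity steps. As described, they are recorded only while participants pick their own foot, so a device comparison on them reflects self-selected use. It is undefined for a foot that was never worn.

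**Working it through.** The article states no figure on this point, so there is none to reproduce. The check has two parts.

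**1. Sources set side by side**

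| Element | Source as described | Period |
|---|---|---|
| Preference, Visit 6 | activity time per prosthesis | 30-day free choice |
| Preference, Abstract and Study Overview | activity monitoring plus interview | 30-day free choice and closing visit |
| Outcome of the prediction model | preference, definition not named | not stated |
| Functional predictors | visit battery | visits 3 to 5 |
| Biomechanical predictors | gait laboratory | visits 3 to 5 |
| Activity predictors | not stated; only the step monitor and activity log are described | 30-day free choice, by inference |

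Functional and biomechanical predictors are measured before the free-choice period on an assigned foot, so they do not overlap with the outcome. Only the activity domain can, and through it the combined model.

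**2. How strong the built-in prediction could be**

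Suppose preference is the device with the largest activity time. This rule is an assumption; the article says only that preference is based on activity time. Let a device's share be its time divided by the total over three devices. A share above 1/2 must be the largest. A share below 1/3 cannot be. Only shares between 1/3 and 1/2 leave any doubt. If all three times enter a model, they fix the outcome exactly.

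For the size, an illustrative simulation was run: 100 participants, three devices, 2,000 repetitions, no true device effect. Its inputs other than N = 100 and three devices are assumptions.

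- Activity time: T_ij = exp(b_i) × exp(e_ij), with b_i and e_ij normal, mean 0, SD 0.5 each.
- Outcome: y_i = 1 if the third device has the largest T_ij, otherwise 0.
- Steps: S_ij = T_ij × exp(u_ij), with u_ij normal, SD 0.2 or 0.5.
- C = [R1 − n1(n1 + 1)/2] / (n1 × n0), where R1 is the rank sum of the predictor among the n1 participants with y = 1, and n0 is the number with y = 0.

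| Reading of the activity predictor | Mean C | 2.5th to 97.5th percentile |
|---|---|---|
| Device share of activity time | 0.987 | 0.969 to 0.998 |
| Device share of steps, SD 0.2 | 0.946 | 0.896 to 0.982 |
| Device share of steps, SD 0.5 | 0.828 | 0.743 to 0.903 |
| Activity time on the device | 0.760 | 0.655 to 0.855 |
| Participant's total over all devices | 0.502 | 0.386 to 0.623 |
| Intensity measure independent of time | 0.498 | 0.378 to 0.622 |

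The first four rows are device-specific amounts of use. They appear to predict well although no device is truly better. The last two rows show no built-in prediction. The problem therefore depends on how the activity variable is defined.

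**The case against.** The best defence has four parts.

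- The definitions may be compatible: activity time could be the behavioural component and the interview the stated component of one overall preference, with the combining rule left to a fuller document. A missing rule alone would not be a finding in a condensed article. What remains is that the article itself gives activity time as the basis in one place and both sources in two others, and its modelling section points to none of them.
- The article never says that the activity predictors come from the 30 days, and the domain is listed only as an example. This is correct. The shared source is an inference, though it is the only source described.
- The one activity metric the article names is a percentage at high intensity, which need not be circular. The simulation supports this where intensity is independent of time, and that independence is itself assumed. The defence shows that the problem is conditional; it does not exclude device-specific use from the model.
- Observed use is a legitimate endpoint, and stated preference from unblinded participants has its own bias. This stands, so the fix should not force stated preference on every model.

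On high-activity steps, the article nowhere presents them as a randomized comparison, and the visit flowchart is not shown. Monitoring during acclimation can therefore not be ruled out; it is simply not described.

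**Conclusion.** The point holds in a conditional form. The outcome of the guideline model has two stated bases and the model does not choose between them. If it uses activity time, and if the activity predictors are device-specific amounts from the same 30 days, the activity-domain and combined models predict largely by construction. Under the simulation's assumptions the C-statistic is then about 0.76 to 0.99 with no true device effect, against 0.50 for activity measures that are not tied to use of a particular foot.

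A reader might infer more than the documents support:

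- That the whole prediction exercise is circular. It is not: the functional and biomechanical domain models use data from visits 3 to 5.
- That activity time conflicts with a purely interview-based definition. No such definition exists; the alternative combines both sources.
- That the C-statistic would be 1.0. This is the worst case, reached when the times for all devices enter and the largest time decides preference.

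The high-activity row in Table 2 is a smaller matter. As described, its device contrast is self-selected and does not have the protection of the randomized order.

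**What to change.** 1. State one definition of preference for the prediction model, including what is done when activity and interview disagree, and bring the Abstract, Study Overview and Visit 6 sections into line with it.
2. Whenever preference is based on activity time, exclude same-period device-specific use (time, steps or share) from the predictors. Alternatively, take interview-stated preference as the outcome in any model that contains activity predictors.
3. Report the agreement between activity-based and stated preference, for example with kappa.
4. Label the device comparison on high-activity steps as non-randomized, or remove the row from Table 2.

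The cost is wording and minor analysis work. The article places analysis of the full data set after final data collection, so the changes can be made before it. No added monitoring is proposed: collection began in 2018 and was expected to end before July 2023, and participants who have finished cannot be measured again under assigned use.
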